### Data to be collected

The frequency and scope of study visits are detailed in Fig 1. The Study Flow Chart is depicted in Fig 2.

**Fig 2 pone.0337999.g002:**
[figure not shown]
Study Flow Chart.

Inclusion/Exclusion Criteria: Criteria determining whether a patient can participate in the study.

Informed Consent: The patient will be asked to give their written informed consent. In case they are unable to provide legal consent, i.e., due to cognitive impairment, an authorized caregiver will be asked to decide about study participation.

Baseline Characteristics: Initial patient data collected at baseline: age, sex, past medical and surgical history according to standard of care.

Charlson Comorbidity Index (CCI) (documented at baseline): A method to collate comorbidities of patients into a score that categorizes their overall severity. Each condition is assigned a score of 1, 2, 3 or 6, depending on the risk of dying associated with each one. Additionally, age is incorporated as a risk factor: patients receive 1 additional point for each decade over 50 years of age (i.e., 50–59 years = +1, 60–69 = +2, 70–79 = +3, ≥ 80 = +4).

### 
Recruitment status

Enrolment is anticipated to begin in the 3^rd^ quarter of 2025. We estimate recruitment completion (last patient in) by late 2027, given the enrolment target of 322 and the number of sites. The 6-month follow-up of the last patient should be completed by mid-2028. Thus, we expect the primary analysis to commence in Q3 2028, with results reported in late 2028. These timelines may be adjusted depending on actual recruitment rates.

Neurological Exam: Assessment of the patient’s neurological status to screen for neurological deficits caused by spinal cord injury from the odontoid fracture or other pathologies, according to standard of care.

Randomization: Patients will be randomized to either the conservative or surgical group according to a predefined process.

CT Cervical Spine: A computed tomography (CT) of the cervical spine will be obtained at the baseline visit to determine the fracture type and its dislocation measured in mm, and at Visits 3 to check for the presence of fracture healing (both groups), secondary dislocation in mm (both groups) and integrity of the implant material (surgical group).

Barthel Index (BI): A scale to measure performance in activities of daily living that constitutes the primary outcome in the statistical analysis after 12 weeks.

EuroQol-5D Questionnaire (EQ-5D): A standardized instrument to measure health outcomes, used within secondary analyses to compare the quality of life between groups.

VAS Neck Pain: A standardized instrument for assessing neck pain on a continuous, visually coded scale that is used in routine clinical practice.

Neck Disability Index (NDI)): A questionnaire used to measure neck-specific disability for both groups, constituting the secondary outcome.

Concomitant medications: Categorized by substance class; antidiabetics, anticoagulants, antithrombotic medicine, antiosteoporotic agents (vitamin D3, calcium, bisphosphonates), medication for movement disorders (e.g. Parkinson’s disease, etc.), antidepressants, steroids, and “other”.

Adverse Events (AEs): Monitoring of all AEs and documentation at each visit, with particular attention to safety-relevant adverse events of special interest (AESIs) and serious adverse events (SAEs).

Duration of Surgery: Time taken to complete the surgery (surgical group or cross-over).

Patient or caregiver diary: diary for patients to document daily duration of cervical collar wearing (conservative group).

Readmission to Hospital: Recording if the patient is readmitted to the hospital any time during the study until week 12, i.e., for the management of medical or surgical complications of either treatment.

Crossover to Surgical Group (see crossover visit): Noting if the patient switches from the conservative to the surgical arm due to failure of conservative treatment until week 12. In case of crossover and conduction of surgery, documentation of visits 1 (surgery), 2 (discharge) and 4 (6 months), after which the study concludes for the crossed patient.

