**Methods:**

SCORE is a multicenter, parallel-group, randomized controlled non-inferiority trial enrolling 322 patients aged ≥70 years with acute (≤2 weeks) unstable odontoid Type II, III, or atypical fractures. Participants will be randomized 1:1, stratified by center, to receive surgical stabilization via posterior C1–C2 fixation or conservative management with a rigid cervical collar. The primary outcome measure is the change in Barthel Index (BI) from baseline to 12 weeks. Secondary outcomes include quality of life (EQ-5D), neck pain (Visual Analog Scale, VAS), neck disability (Neck Disability Index, NDI), radiographic fusion, treatment compliance, cross-over rates to surgery, and incidence of adverse and serious adverse events up to 6 months. Follow-ups will take place at 12 weeks and 6 months post-injury, with an additional visit at approximately 2 weeks post-surgery for surgical patients. Analysis will use mixed models for repeated measures, targeting 90% power to detect non-inferiority within a 5-point margin on the BI (one-sided α = 0.025), accounting for 15% attrition.

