### Measures taken (surgical and conservative treatment)

The surgical intervention is a surgical fracture stabilization with a posterior screw-rod system and represents an established surgical treatment according to standard of care for OFs [3,13,14,20,40,41]. The routine surgery commonly lasts approximately 100 minutes and requires a hospital stay of about 6 days [42,43]. An additional external bracing in the postoperative setting is not required. The surgery is tailored specifically towards geriatric insufficiency fractures of the odontoid, which makes stabilization with a screw-rod-construct from a posterior approach a necessity to achieve adequate stability for this patient population. We deliberately exclude the possibility to conduct an anterior fusion by odontoid screw fixation as described by Böhler, which has been shown to be a biomechanically insufficient treatment particularly in geriatric patients [6,15,23,44,45].

The conservative intervention also aims for immobilization, but via an external collar. A typical detriment of the conservative intervention in everyday practice stems from its absolute reliance on the patient’s compliance to wearing the collar permanently for at least 12 weeks, which considerably challenges this treatment strategy [22]. This compliance problem is highly relevant to the treatment outcome, although data on compliance rates in the elderly are fairly scarce [17,44,46]. We are aware that the regularity of wearing the brace cannot be verified with certainty, and in probably the majority of cases the collar is not worn permanently against the physician`s recommendation due to relevant side effects. Therefore, the adherence to therapy will be assessed via a patient diary in which the hours of wearing the collar will be documented. However, this will reflect the everyday reality and belongs to a real-life representation of the conservative therapy regimen.

Over the course of this study, patients of the conservative group can undergo surgical intervention, if requested by the patient or advised by the treating physician, until week 12. Prior to this crossover surgery, patients are required to attend the crossover visit. After surgery, the patients will be invited to Visit 2 at discharge or 14 days post-surgery at the latest, and to Visit 4 at 6 months.

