### Research ethics approval and consent

This study protocol (version 1.1 dated 12 March 2025) has been approved by the Ethics Committee of the lead study site (Technical University of Munich) with the reference number 2024–630-S-NP. In addition, each participating site’s local Ethics Committee has reviewed and approved the protocol prior to initiating the study at that site or has accepted the lead site’s approval in a multi-center framework. No patients will be enrolled at a site until that site has obtained the necessary ethical approval.

All participants (or their legal representatives) provide written informed consent before any study procedures. The consent form describes the study interventions, that participants will be randomized to one of two standard treatments, and outlines potential risks/benefits. It emphasizes that participants are free to withdraw at any time. Patients are informed that their pseudonymized data will be collected, stored, and used for research, and that monitors/auditors may review their records. Consent for publication of results is included in the consent.

analyses will be applied to the secondary outcomes with pairwise between-group comparisons at 12 weeks and 6 months. The estimated mean and standard error and the 95% confidence interval (CI) for the mean treatment effect will be reported for each follow-up time point. Differences between surgical and non-operative treatments will be assessed by estimating the main effects of treatment as well as time-and-treatment interactions. For binary outcomes generalized estimating equations will be used. Treatment effects will be estimated as differences in estimated proportions. Each estimated outcome score will be plotted by treatment group to illustrate change over time. No adjustments will be made for multiple comparisons.

Sensitivity analysis of the primary endpoint will be done by repeating the primary endpoint analysis “as treated” by counting each patient who was treated surgically in the surgical group, regardless of whether they were assigned to the surgical group or crossed over at a later time point.

Adverse events will be coded with MedDRA prior to analysis.

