Primary and secondary analyses will use all available data at the pre-determined time points. The extent of missing data will be calculated at each time-point. Patients with missing data at the 3-month time point will be compared to those who participated in all visits. Variables asso-ciated with missing data and baseline characteristics will be included as covariates in the mixed model as a further sensitivity analysis of the primary endpoint. Additionally, multiple im-putations will be used on data for each outcome measure at each time point. The results will be presented as adjusted mean or percentage and treatment effect including 95% CI from the 10 iterations.

No interim analysis for efficacy is planned, so the study will continue until full enrolment is reached or unless stopped early for safety or futility by recommendation of the SMB.

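### Collar patients operated on before week 12 enter the fusion analysis as ordinary missing data, so the collar arm's healing rate is likely overstated against a rate that counts failure as not healed

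*Protocol article*

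**What the plan says.** Radiographic fusion is a secondary outcome (Abstract, Methods). Under Data to be collected, the CT item schedules a scan at baseline and "at Visits 3 to check for the presence of fracture healing (both groups), secondary dislocation in mm (both groups"). The Abstract gives the timing: "Follow-ups will take place at 12 weeks and 6 months post-injury, with an additional visit at approximately 2 weeks post-surgery for surgical patients". Visit 2 is discharge and Visit 4 is 6 months, so Visit 3 is the 12-week visit by order.

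Two places set the visits of a collar patient who is operated on before week 12, and neither lists Visit 3:

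- Measures taken, on what follows the operation: "the patients will be invited to Visit 2 at discharge or 14 days post-surgery at the latest, and to Visit 4 at 6 months".
- The crossover item under Data to be collected: "documentation of visits 1 (surgery), 2 (discharge) and 4 (6 months), after which the study concludes for the crossed patient".

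The crossover item describes the event as "Noting if the patient switches from the conservative to the surgical arm due to failure of conservative treatment until week 12". Measures taken is wider and also allows the surgery at the patient's wish or on the physician's advice.

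The rules for secondary outcomes are printed under the heading Research ethics approval and consent, where the statistical text continues. "For binary outcomes generalized estimating equations will be used", with effects as differences in proportions. Primary and secondary analyses use the available data. In addition, multiple imputation "will be used on data for each outcome measure at each time point". The crossover rule in Table 1 (last value before surgery) and the as-treated sensitivity analysis both concern the Barthel Index only.

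**The concern.** The patients who miss the healing CT because of crossover are not a random part of the collar arm. On the crossover item's own description, they are those in whom the collar failed. Available-case analysis removes them from the denominator. Imputation under a missing-at-random model predicts their healing mainly from collar patients who were not operated on. Neither route lets an operation for collar failure count against the collar.

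Crossover runs in one direction only, from collar to surgery, so this loss falls on one arm. Non-union is the collar risk named in the Abstract. The sample size assumes no difference in the Barthel Index, so if non-inferiority is shown, readers will look to secondary outcomes such as fusion to choose between treatments. A fusion comparison tilted towards the collar would then matter.

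**Working it through.** **Figures in the article.** The article states no expected fusion rate and no crossover rate, so there is no fusion figure to reproduce. Its sample size (137 per arm for 90% power, margin 5, SD 12.7) reproduces: the noncentral t gives power 0.901 at 137. With 15% dropout, 137/0.85 = 161.2, against the stated 161 per arm. This concerns the Barthel Index. Only the arm size of 161 is used here.

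**Inputs.**
- N = 161 collar patients (Sample size calculation).
- c = share crossing over for failure before week 12. Assumed 10%, 20% or 30%, that is 161 × c ≈ 16, 32 or 48 patients.
- h = healing among collar patients who have a Visit 3 CT. Assumed 15% to 80%. The low end corresponds to the Background's non-union rate of up to 85% (1 − 0.85 = 0.15), which is not specific to the collar.
- g = healing rate assigned to the crossovers.

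**Formulas.**
- Rate under the stated rules (available cases, or imputation at random within the arm): h.
- Rate with crossovers assigned g: (1 − c)h + cg.
- Gap: c(h − g). If failure counts as not healed, g = 0 and the gap is h × c.

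**Gap in percentage points, g = 0.**

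| h | c = 10% | c = 20% | c = 30% |
|---|---|---|---|
| 15% | 1.5 | 3.0 | 4.5 |
| 30% | 3.0 | 6.0 | 9.0 |
| 50% | 5.0 | 10.0 | 15.0 |
| 70% | 7.0 | 14.0 | 21.0 |
| 80% | 8.0 | 16.0 | 24.0 |

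**Hypothetical reading.** Suppose the target is healing had these patients stayed in the collar. If they would have healed half as often as the others (g = h/2), the gap halves: at h = 50% and c = 20% it is 0.20 × (0.50 − 0.25) = 5 points. If they would have healed equally often (g = h), the gap is zero.

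**Do both stated routes agree?** A simulation with N = 161, h = 50% and 10 imputations drawn within the arm gave a collar healing rate of 0.500 for available cases and 0.500 for imputation, at each c. Counting crossovers as not healed gave 0.450, 0.401 and 0.350 at c = 10%, 20% and 30%. Under this simple imputation model, the added analysis does not correct the first one.

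**The case against.** The strongest reply is that this is an unstated intercurrent-event rule for a secondary outcome, which an article may leave to the analysis plan. That would be decisive if the article were silent. It is not: it fixes available data, generalized estimating equations, and imputation of every outcome, with no exception for crossover. Followed as written, those rules produce the result above.

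Several limits do stand:

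- **Not every crossover is a collar failure.** Measures taken also allows surgery on request. A reader might infer from the crossover item alone that all are failures, but the two passages differ and must be reconciled.
- **Imputation is additional and its model is not given.** A reader might take it as the main mechanism. The first-named analysis drops these patients, and a richer imputation model could narrow the gap.
- **Overstatement depends on the target.** Table 1 uses a hypothetical strategy for the primary outcome. If fusion follows it, counting crossovers as not healed is a different estimand, and bias remains only if crossovers would have healed less often.
- **A further CT cannot be excluded.** The visit figures are not shown, the CT item's wording is plural, and the content of the crossover visit is not visible. The text therefore does not support saying that these patients have no CT at all, or that no 6-month CT exists. A CT at Visit 4 would, however, show an operated fracture.
- **The surgical arm may lose readings too.** Table 1 expects refusal of therapy and about 10% deaths, without limiting either to one arm.
- **The crossover rate is itself reported.** Readers can set it beside the fusion rate, but they would have to combine the two themselves.

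**Conclusion.** The point holds for radiographic fusion. The stated rules drop or impute, as ordinary missing values, a group of collar patients whom the article describes as treatment failures. The collar arm's healing rate is therefore likely overstated relative to one that counts failure as not healed.

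The size cannot be derived from the article. The range of 1.5 to 24 points rests wholly on assumed h and c, and it shrinks under a hypothetical reading in which some crossovers would have healed. A reader might be tempted to use the Discussion's 50–60% collar failure as c. That figure describes failure through not wearing the collar where nursing support is absent, and is not a crossover rate.

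A reader might also extend the point to the non-inferiority test. The documents do not support that: the Barthel Index has its own crossover rule, and its analysis does not use the CT. Secondary dislocation is read at the same visit, but the visible text schedules no scan before crossover surgery, so it does not settle a rule for that measure.

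**What to change.** 1. Define the outcome as *fracture healed at week 12 under the allocated treatment*.
2. Count a collar patient operated on for failure before week 12 as not healed. Count a surgical patient revised for failure before week 12 the same way.
3. Keep these patients out of the imputation of fusion, because their outcome is then known by definition.
4. Record the reason for each crossover, reconcile the two descriptions of when crossover occurs, and add a sensitivity analysis that does not count request-only crossovers as failures.
5. Report fusion regardless of crossover as a supportive result, where a CT exists.

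The cost is wording in the outcome definition and analysis section plus one recorded item. No new scan and no change in care is needed. The downside is that the outcome becomes a composite of healing and treatment failure, and its quality depends on how well the crossover reason is recorded. The rule should be fixed before outcome data are examined, since any later choice could look chosen by result.

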### Overall duration of the study

The first patient will be included approximately in the 2^nd^ quarter of 2025 and the last patient approximately in the 4^th^ quarter of 2027. Accordingly, the last patient will exit the study (‘last patient last visit’) approximately 2^nd^ quarter 2028.

### Randomization

After giving informed consent, patients are randomized to study arms during the baseline visit using randomizer.at, an online-randomization tool. Randomizer.at uses pre-defined randomization algorithms which are tailored to our study needs. Allocation occurs on demand in a 1:1 ratio, stratified by study center using permuted blocks. Assignment to the study arm is concealed and only revealed at the time of randomization through the password-protected, secure website.

### Sample size calculation

Assuming a non-inferiority study design with a one-sided α = 0.025, we set the expected difference in change of BI scores between the two groups to 0. Unnanuntana et al. (2018) show that the minimal clinically important difference (MCID) of the BI in elderly patients after a surgical intervention is 9.8 [48]. Bouwstra et al. (2018), conclude the smallest detectable change in BI in a geriatric nursing home population to be 3.0 [32]. It is common practice to choose a non-inferiority margin for a patient-reported outcome such as the BI, which is lower than the MCID, see Copay et al [49]. Thus, we set the non-inferiority margin to 5, which is closer to the smallest detectable change than to the MCID and therefore more conservative. The standard deviation of the difference in BI between baseline and week 12 was estimated at 12.7 referencing prior work by Unnanuntana et al [48]. Based on these assumptions, a sample size of 137 in each group (274 in total) will have 90% power to reject the null hypothesis of the one-sided 2.5% significance level t-test that the surgical group is inferior to the conservative group in favor of the alternative hypothesis that the surgical group is non-inferior to the conservative group. Assuming a drop-out rate of 15%, a total of 322 patients will need to be included (161 per arm).

### Statistical analyses

Analysis will be performed on all patients who were randomized to the study. The primary estimand and its attributes are described in Table 1.

**Table 1 pone.0337999.t001:** Definition of all five attributes used to construct the primary estimand for the SCORE study (non-inferiority setting).

Primary estimand	
**Population**	Geriatric patients with recent type II & III odontoid fractures (as defined by trial inclusion/exclusion criteria).
**Variable**	Functional status accessed as the change in Barthel Index (BI) between baseline and 12 weeks thereafter
**Treatment**	• Surgical stabilization C1-2 by dorsal screw-rod construct (duration of treatment: Approximately 100 min + approximately 6 days hospital stay) or • Conservative therapy by external cervical collar immobilization (duration of treatment: 12 weeks)
**Population-summary measure**	Mean difference, including 95%CI.
**Intercurrent event (IE) and strategy**	• Refusal of therapy as randomized – multiple imputations (hypothetical estimate) • Crossover from the conservative to the surgical arm after randomization but before week 12 – use the last available BI value before surgery as best estimate of the hypothetical BI value at week 12 *Note: Cross-over from the conservative to the surgical arm after week 12 is allowed, as it does not influence the primary variable, which is measured at week 12* • Loss to follow-up after start of therapy – multiple imputations; missing at random assumed • Death – (expected ca. 10%) multiple imputations (hypothetical estimate)

Intercurrent events (IEs) will be dealt with using a hypothetical strategy to determine the treatment effect without the abovementioned IEs.

The primary endpoint will be tested using a mixed model for repeated measures (MMRM) of BI, where treatment, time, their interaction, baseline BI scores, age, and CCI will be fixed covariates, and study center will be a random covariate. In case the model does not converge due to small centers, the covariate center will be abandoned. The adjusted mean difference between groups in the primary outcome will be tested at the 12-week time point.

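### Carrying the last pre-surgery Barthel Index forward to week 12 for crossovers fits the hypothetical estimand only if the score would have stayed flat; the bias is confined to one arm and its direction is unknown

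*Protocol article*

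**What the plan says.** Under Statistical analyses, the protocol article states one strategy for all intercurrent events: hypothetical, meaning the treatment effect had the events not occurred. Table 1 then gives a rule for each event.

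- **Crossover to surgery before week 12:** "use the last available BI value before surgery as best estimate of the hypothetical BI value at week 12".
- **Loss to follow-up:** "Loss to follow-up after start of therapy – multiple imputations; missing at random assumed".
- **Refusal of the assigned therapy, and death:** multiple imputation, labelled hypothetical.

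Three other places bear on the crossover rule.

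- **Measures taken** allows crossover only from collar to surgery, at the patient's wish or on the physician's advice, up to week 12. It requires a crossover visit before the operation.
- **Data to be collected** attributes the switch to conservative treatment having failed. For crossed patients it lists visits 1, 2 and 4, so no week-12 visit.
- **The sensitivity analyses** (printed partly under Research ethics approval and consent) are an as-treated regrouping, extra covariates related to missingness, and multiple imputation of each outcome. None is stated to vary the carried-forward value.

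**The concern.** A hypothetical estimand asks what the crossed patient would have scored at week 12 had the collar been continued. A score taken before surgery answers that only if function would have stood still from then on. The article gives no reason to expect this, and its Background names restoring pre-injury mobility as the aim of treatment.

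The exposure is asymmetric. Only the conservative arm can cross over, so an error in the carried value does not cancel between arms and passes directly into the difference tested against the margin.

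Which score is carried is also unclear. The Abstract lists follow-up at 12 weeks and 6 months, plus a visit about two weeks after surgery for surgical patients. For a crossover, the only listed chance of a BI between baseline and surgery is therefore the crossover visit. The visible text does not say that BI is recorded there. If it is, that score is carried. If it is not, the baseline is carried and the primary variable is 0 by construction.

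Finally, the carried score enters the model as though it had been observed, so the standard error ignores the uncertainty about it.

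**Working it through.** **Inputs from Sample size calculation.** One-sided α is 0.025 and the expected difference is 0. Also: "Thus, we set the non-inferiority margin to 5"; "The standard deviation of the difference in BI between baseline and week 12 was estimated at 12.7"; "a sample size of 137 in each group (274 in total) will have 90% power to reject the null hypothesis".

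**The plan's own figure.** The normal approximation gives n = 2 × (1.960 + 1.282)² × 12.7² / 5² = 135.6, so 136 per arm. The noncentral t calculation gives 137 per arm with power 90.1%. Then 274 / 0.85 = 322.4, against the stated 322. The sample size reproduces and is not in question.

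**Standard error.** SE = 12.7 × √(2/137) = 1.534. This is the unadjusted comparison at the planned evaluable number.

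**Bias.** Let f be the share of the conservative arm that crosses over before week 12. Let g be the hypothetical week-12 BI under the collar minus the carried value, averaged over crossovers. Carry-forward understates the conservative mean by f × g and so overstates surgery minus conservative by f × g.

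The documents give neither f nor g, so both are assumed. The gaps used are 5 points (the size of the margin) and 9.8 points (the minimal clinically important difference the plan cites, used only as a yardstick).

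**Crossovers would have recovered further (g > 0).** Type I error at the margin = Φ(f·g/1.534 − 1.960).

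| f | g | Shift f·g | One-sided type I error |
|---|---|---|---|
| 5% | 5 | 0.25 | 3.6% |
| 10% | 5 | 0.50 | 5.1% |
| 20% | 5 | 1.00 | 9.5% |
| 5% | 9.8 | 0.49 | 5.0% |
| 10% | 9.8 | 0.98 | 9.3% |
| 20% | 9.8 | 1.96 | 24.7% |

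A smaller gap of 3 points gives 3.1%, 3.9% and 5.8% at 5%, 10% and 20% crossover. The shift that doubles the error to 5% is (1.960 − 1.645) × 1.534 = 0.48 points, about a tenth of the margin. The shift that gives 10% is (1.960 − 1.282) × 1.534 = 1.04 points.

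**Crossovers would have declined (g < 0).** Power at a true difference of 0 = Φ((5 − f·|g|)/1.534 − 1.960).

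- f = 10%, |g| = 5: Φ(4.50/1.534 − 1.960) = 83.5%.
- f = 20%, |g| = 9.8: Φ(3.04/1.534 − 1.960) = 50.8%.

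The starting point is 90%.

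**Uncertainty ignored.** Suppose the carried value were right on average and correlated ρ with the hypothetical week-12 change.

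- SE as computed: 12.7 × √{[(1 − f) + f·ρ²]/137 + 1/137}.
- SE that counts the uncertainty: 12.7 × √{(1 − ρ²)/[137(1 − f)] + ρ²/137 + 1/137}.

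With ρ assumed between 0.7 and 0.5:

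- f = 10%: 1.515 against 1.556 (ρ = 0.7) and 1.505 against 1.566 (ρ = 0.5); actual α 2.8% to 3.0%.
- f = 20%: 1.495 against 1.583 (ρ = 0.7) and 1.476 against 1.605 (ρ = 0.5); actual α 3.2% to 3.6%.

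The shift in the mean can therefore matter far more than the understated variance.

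**The case against.** The best defence is that crossover is preceded by a required visit. If BI is recorded there, the carried score is recent, and for a late crossover the remaining gap may be small. The visit schedule is in figures that are not shown, so a carried baseline with a change of exactly 0 is only one possibility. This stands, and it is why small gaps belong in the range.

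Three stronger readings are tempting, and the documents do not support them.

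- **The rule tilts the trial towards surgery.** A reader might infer this because geriatric patients are expected to recover over 12 weeks. But the article describes crossover as following failed conservative treatment, while also allowing it at the patient's wish. Worsening under a continued collar is as plausible as recovery, and the rule would then work against surgery.
- **Crossover will be very common.** The Discussion puts failure of conservative treatment at 50–60%. That figure concerns non-compliance with the collar without nursing support; it is not a crossover rate.
- **The single imputation alone badly inflates the error.** By itself it moves α only to about 2.8–3.6% in the cases computed.

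The defence might also point to the planned sensitivity analyses. The as-treated analysis regroups patients by treatment received, which gives up the randomised comparison, and crossed patients have no listed week-12 BI for it to use. The general multiple imputation is not tied to crossovers. Delta-adjusted analyses may be in a statistical analysis plan that is not shown, and their absence here is no fault. The point concerns the primary rule, which the article does fix.

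**Conclusion.** The concern holds as a mismatch between estimator and estimand. The article fixes a rule that is unbiased for its hypothetical estimand only if BI is flat on average from crossover to week 12. The rule acts in one arm, counts no uncertainty, and departs without explanation from the multiple imputation used for the other three events.

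The sign and size of the bias cannot be determined from the documents. Across the assumed crossover shares of 5–20% and gaps of 3–9.8 points, one-sided type I error runs from 3.1% to 24.7% if recovery is cut off. In the two cases of decline shown, power is 83.5% and 50.8%. These figures rest on the plan's SD and evaluable number and on an unadjusted comparison. They show that a shift of about half a point is enough to matter; they do not predict the trial's result.

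**What to change.** In the crossover row of Table 1, set BI after crossover to missing. Multiply impute the week-12 value within the conservative arm from baseline BI, age and CCI, in line with the other intercurrent events. Crossover-visit BI and its timing cannot usefully drive this model: the text lists no interim visit for collar patients who do not cross over, so the arm offers no data linking such a score to week 12.

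Add a delta-adjusted (tipping-point) analysis that shifts the imputed crossover values in both directions. Crossovers may be failing patients, so missing at random is doubtful, and imputing from those who stayed in the collar may overstate their scores. Keep the carried-forward value as a sensitivity analysis, and state whether BI is recorded at the crossover visit.

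The cost is one table row with matching analysis text, and a slightly wider confidence interval. The planned sample size need not change.

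An as-randomised analysis using BI measured at 12 weeks would be a useful companion. It is a separate and larger change, because a week-12 BI would have to be added to the visits listed for crossed patients. It needs an early decision, since values not collected cannot be recovered.
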